### Intervention

The intervention will be delivered at cluster level. The intervention consists of personalizing self-management support using the results of the SeMaS questionnaire. The results are represented in a report with a graphic profile of the patient and tailored advice to enhance self-management, as described in a manual.

### Training and support of practice nurses in the intervention arm

Intervention practice nurses and GPs will receive a two-hour training session before starting the trial, consisting of a brief introduction to the SeMaS, demonstration of a consultation with a SeMaS report and skills practice using role play. The practice nurses will be specifically instructed on the options for personalized self-management support, such as the creation of individual care plans, options to influence the barriers for self-management, and the referral to self-management interventions. During the training, the practice nurses will receive a manual that indicates which profiles are suitable for self-management, which are suitable with minor barriers, and which are unsuitable for self-management at this time. The manual also contains the instructions for personalized self-management support.

Subsequently, intervention practices will be visited to provide further support in working with the SeMaS. The user manual and examples of reports with suggestions for personalized self-management support will be discussed.

### Self-management support

During the study period, practice nurses of the intervention arm will receive a report with the profile of the patients who filled in the questionnaire. Patients will also receive tailored feedback. Practice nurses are instructed to adjust the delivery of care to the profile. For each factor the manual provides advice to help support the patient in case of a barrier. For example, when a patient experiences low social support, the practice nurse and the patient search for additional social support, or find ways to cope with this low support. For a patient with low self-efficacy, the advice is to set a goal with the patient with a high chance of success, to foster the self-efficacy. When patients show major barriers for self-management, the manual gives instruction and support for the practice nurse to work on this barrier before starting with self-management activities.

When no barrier is present, the practice nurse is advised to create an individual care plan with the patient, and refer to the self-management interventions, if applicable. Also, the manual contains a card with the possible self-management interventions, categorized by the skills that are asked about in the SeMaS questionnaire (computer, group, self-care). The manual was developed by the research team and reviewed by the stakeholders group. The advice was based on the method of actual practice and maintenance, which is used in the care group.

Control practices will deliver care as usual, and will receive the training one year later. Care as usual may include the use of an individual care plan or referral to the self-management interventions, as this is available for the entire care group. Patients will be invited in the same inclusion period as in the intervention arm. They will be asked to fill in the questionnaire, without feedback to themselves or their practice nurse.

### Outcomes

The primary outcome is the difference in patient activation score between baseline and six months between the intervention and control arm, using the PAM-13 [23]. The PAM-13 is an interval-level, uni-dimensional, Guttman-like measure. In the study of Greene and Hibbard the average PAM score was 66.4 (SD 15.4; n = 25,047) [34].

We expect that using the SeMaS instrument will lead to more effective self-management support. Also, we expect that patients will adhere better to the self-management interventions, as they are referred based on the SeMaS profile. To measure whether the self-management support is more successful in the intervention arm than in the control arm, we will perform medical-record data analysis. The outcome measures include the number of completed individual care plans, the number of patients performing self-monitoring, the number of referrals to self-management interventions (group courses and internet coaches), and adherence to these interventions, the number of referrals to informative websites, and the number of consultations in the general practice and emergency care in the study period. We will assess how these data relate to the results on the SeMaS questionnaire at baseline.

Furthermore, we expect that patients who receive personalized self-management support, will be more able to improve their lifestyle than patients receiving care as usual. Lifestyle factors will be measured with the rapid assessment of physical activity (RAPA) and the rapid eating assessment for participants-short (REAP-S) [35,36]. Smoking behavior will be measured with the 10-item Behavior Change Consortium questionnaire [37]. The difference in the score per lifestyle behavior between baseline and time (T)1 will be calculated to assess the change in lifestyle behavior. The secondary outcome measures are defined as the difference in the average score between control and intervention at T0 and T1 for the RAPA and REAP-S questionnaires. For smoking, the outcome is defined as the difference between the numbers of patients smoking in the control and intervention arms at T0 and T1.

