All 15 general practices of the DOH will participate in the trial. We recruited the practices through the DOH cooperation. The practice nurses will receive training in working with the SeMaS. As mentioned, we will perform randomization at the cluster level. Furthermore, as the ability of the practice nurse to influence the self-management behavior of the patient can affect the study results, we dichotomized practices into two equal groups using the percentage of practice nurses in the practice that participated in the behavioral change training [29]. Also, practices were dichotomized in two equal groups using the volume of practice nurses corrected for practice size, as the workload can affect the study results as well. This resulted in four strata. For each stratum, a separate two-block randomization list was produced to randomize the practices to the control or intervention arm [33]. Two practices were coupled in the randomization procedure to prevent contamination, because one practice nurse worked in both practices. The final allocation of practices is shown in Table 1.

**Table 1 T1:** Randomization strata and the number of practices per stratum of the SeMaS study

	**Low participation in behavioral change training**		**High participation in behavioral change training**	
	**Intervention**	**Control**	**Intervention**	**Control**
Low volume of practice nurses	2	1	2	2
High volume of practice nurses	1	3	2	2

Volume of practice nurses: the number of full time equivalents divided by the number of patients in the practice. Participation in training: percentage of the practice nurses who attended the training for behavioral change to enhance self-management that was provided in 2011 [29]. SeMaS, self-management screening questionnaire.

A representative of the care group DOH consented with participation in the study for all practices. After performing the randomization procedure, we informed the practices about participation in the study.

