### Sample size

Sample size calculations have been made using the results from three studies on the primary outcome measure, PAM-13 [17,34,39]. In these studies, improvements in PAM scores after intervention vary from 4% to 8% (SD 12 to 17). Based on these studies, we expect to find a difference in PAM score of 6% (SD 14.0) in this study. For the power calculations, we assume an intraclass correlation coefficient (ICC) of 0.05 based on the article of Campbell *et al*. [40]. This article states that an ICC of 0.0 to 0.5 is normal for outcomes in primary care research. To reach a power of 80% and alpha of 0.05, and considering ICC of 0.05, at least 25 patients per practice are needed when using 15 practices. With an expected dropout rate of 33%, 33 patients would be needed per practice, thus, 495 in total. Our secondary outcomes comprise lifestyle measures that will not be applicable to every patient, such as smoking. Therefore, we strive to include 50 patients per practice. Thus, 750 patients will be included in total.

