### Analysis

We made an *a priori* analysis plan for the primary analysis of the data, including details about the primary and secondary outcomes, covariates, treatment of missing values, and planned analyses. The outline of the analysis plan will be described here. The primary analysis will be an intention-to-treat analysis to test the hypothesis that patients who received personalized self-management support will be more activated than patients who did not receive personalized self-management support, expressed by the PAM-13 score. Secondary analyses will test the hypothesis that patients who received personalized self-management support will be more able to change their lifestyle in a positive way than patients who did not receive personalized self-management support, as measured with the RAPA, REAP-S and 10-item Behavior Change Consortium questionnaire.

Using analysis of covariance (ANCOVA) (that is, multilevel linear regression with the follow-up score as the outcome and the baseline score as a covariate), the difference in scores on PAM-13 in the subgroups at T = 0 and T = 6 months will be examined in the control and intervention arm. Subsequently, we will analyze the impact of the intervention on predefined subgroups as measured by the SeMaS. We defined three subgroups: patients who are ready for self-management, patients who can undertake self-management with minor barriers, and patients with severe barriers to self-management, by calculating an overall score on the SeMaS questionnaire.

Each secondary outcome will be analyzed with a multilevel multivariate covariance regression model, with the analyst blind to practice allocation to trial arms. Covariates that will be controlled for are: age, gender, chronic condition (from the medical-record data), social support (as measured with the SeMaS), diagnosis of depression based on the International Classification of Primary Care (ICPC) code and health literacy (as measured with the Short Test of Functional Health Literacy in Adults (S-TOFHLA)) [41,42], and the baseline scores. All statistical analyses will be performed using SPSS software (version 20, IBM Corp.), SAS (version 9.2, SAS Institute Inc.) or MLWIN (version 2.28, University of Bristol).

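### Smoking is defined by counts of smokers, which differ between arms of 7 and 8 practices without any effect and do not match the regression planned for it

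*Protocol article*

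**What the plan says.** All references are to the protocol article.

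- **Outcomes, smoking:** "the outcome is defined as the difference between the numbers of patients smoking in the control and intervention arms at T0 and T1".
- **Outcomes, all lifestyle measures:** "The difference in the score per lifestyle behavior between baseline and time (T)1 will be calculated to assess the change in lifestyle behavior".
- **Outcomes, RAPA and REAP-S, in the sentence that follows:** "The secondary outcome measures are defined as the difference in the average score between control and intervention at T0 and T1".
- **Analysis:** "Each secondary outcome will be analyzed with a multilevel multivariate covariance regression model". The covariates listed there are patient characteristics together with the baseline scores. The smoking questionnaire is named among the instruments for the secondary hypothesis.
- **Practices:** "The final allocation of practices is shown in Table 1". The cells of that table add up to 7 intervention and 8 control practices.
- **Sample size:** "we strive to include 50 patients per practice", because some lifestyle measures, smoking among them, do not apply to everyone. On attrition: "With an expected dropout rate of 33%, 33 patients would be needed per practice".

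**The concern.** A count of smokers depends on how many patients an arm holds and how many of them return the final questionnaire. In this trial the arms are unequal by design and attrition is expected to be large. The number of smokers can therefore differ between arms, and fall over time within each arm, although nobody stops smoking.

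The definition also does not describe the quantity that the Analysis section would estimate. That section plans a regression on patients that adjusts for baseline. It uses the language of scores and covariance for every secondary outcome, while smoking is tallied as yes or no.

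For RAPA and REAP-S, the sentence that places the between-arm difference at both T0 and T1 can be read as making a baseline contrast part of the outcome. A T0 difference precedes the intervention and cannot be an effect of it.

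These outcomes carry the trial's secondary hypothesis, and they are the reason given for recruiting 750 patients and not 495.

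**Working it through.** **Inputs**

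- Practices per arm (Table 1): intervention 2 + 2 + 1 + 2 = 7; control 1 + 2 + 3 + 2 = 8.
- Patients per practice (Sample size): 50.
- Loss to follow-up (Sample size): 33%.
- Smoking prevalence: not given in the document. Assumed equal in both arms, 10% to 30%.
- Recruitment: assumed equal in every practice.

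The document states no figure for smoking. Its total does reproduce: 7 × 50 = 350 and 8 × 50 = 400, together 750, as in the Sample size section.

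**Step 1. Counts with no effect**

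Smokers at T0 = practices × 50 × prevalence. Smokers at T1, if nobody stops and dropout is unrelated to smoking, = T0 count × (1 − 0.33).

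| Prevalence (assumed) | T0, intervention v control | Difference | T1, intervention v control | Difference |
|---|---|---|---|---|
| 10% | 35 v 40 | 5 | 23.45 v 26.8 | 3.35 |
| 20% | 70 v 80 | 10 | 46.9 v 53.6 | 6.7 |
| 30% | 105 v 120 | 15 | 70.35 v 80.4 | 10.05 |

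The ratio of control to intervention is 8/7 = 1.143 in every row, so the 14.3% excess does not depend on the assumed prevalence.

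**Step 2. The direction depends on the reading**

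At 20% prevalence the T1 count alone looks better for intervention (46.9 v 53.6). The fall from T0 looks better for control: 70 × 0.33 = 23.1 fewer smokers in intervention and 80 × 0.33 = 26.4 fewer in control. Neither reflects anyone stopping.

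**Step 3. Unequal dropout**

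Again at 20% prevalence, with dropout rates assumed for illustration:

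- 38% lost in intervention, 28% in control: 70 × 0.62 = 43.4 v 80 × 0.72 = 57.6, difference 14.2.
- The reverse: 70 × 0.72 = 50.4 v 80 × 0.62 = 49.6, difference −0.8.

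**Step 4. The same data as proportions**

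- T0: 70/350 = 80/400 = 20%.
- T1, equal dropout: 46.9/234.5 = 53.6/268 = 20%.
- T1, unequal dropout as first assumed: 43.4/217 = 57.6/288 = 20%.

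The difference is zero each time, provided dropout is unrelated to smoking.

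**Step 5. Definition against analysis**

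| | Outcomes section | Analysis section |
|---|---|---|
| Smoking | Difference in numbers of smokers, T0 and T1 | Covariance regression adjusted for baseline score |
| RAPA, REAP-S | Change from T0 to T1; then difference in averages at T0 and T1 | Covariance regression adjusted for baseline score |

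For RAPA and REAP-S the two columns can be reconciled by rewording. For smoking they cannot: a difference in counts is not a coefficient of that regression, and the outcome is not a score.

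**The case against.** The strongest reply is that the Analysis section does not compare raw counts. It names one type of model for all secondary outcomes, with age, gender, condition and other patient characteristics as covariates. Such a model takes each patient as the unit, so 350 v 400 patients do not create an effect. This stands. A reader might infer from the definition that the reported smoking result will mix arm size and dropout with cessation. The document does not support that, because the planned model, fitted to patient-level status, would not carry the imbalance in counts into the estimate.

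A reader might also infer that RAPA and REAP-S leave three competing definitions to choose from, none of which fits the analysis. That goes too far. The two sentences in the Outcomes section can be read together as a between-arm difference in change, with T0 as the reference. The Analysis section then settles on one baseline-adjusted model. Only a clarification remains.

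It can further be said that the article gives only the outline of a separate analysis plan, and that the term linear is attached there to the PAM-13 analysis and not explicitly to the secondary outcomes. The choice of link function could sit in that plan. This weakens the point about the model but not the point about the definition. The count is a statement in the article, not a gap.

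Finally, the size rests on an assumed prevalence and equal recruitment, and the 33% loss is itself uncertain: the step from 25 to 33 patients corresponds to a loss of 8/33, about 24%. All of this is fair. It changes the number of smokers in the illustration, but only unequal recruitment would alter the 8/7 ratio at T0.

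**Conclusion.** The smoking outcome is wrong as written. If there is no effect and smoking rates are equal, it shows 14.3% more smokers in control, a T0 difference of 5 to 15 patients at a prevalence of 10% to 30%. Dropout alone lowers the T1 counts. The 14.3% assumes equal recruitment per practice; the absolute figures also assume the prevalence.

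The definition conflicts with the Analysis section. The regression planned there would avoid the count problem if fitted to patient-level status, but a covariance model for scores suits a yes/no outcome poorly. The point therefore concerns a badly fixed definition and a poorly matched model, not an estimate shown to be biased. For RAPA and REAP-S it is a matter of wording only. The primary outcome is not affected. The correction should be made before analysis, since the trial was still recruiting when the article was submitted.

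**What to change.** - **Smoking:** define the outcome as each patient's smoking status at six months, summarised as a proportion per arm. Analyse it by multilevel logistic regression with practice as the cluster and with arm, baseline smoking status, the covariates already planned and the randomization strata.
- **RAPA and REAP-S:** define the outcome as the between-arm difference in the T1 score adjusted for the T0 score, which is what the Analysis section already implies.
- **Baseline:** report T0 values for all three measures descriptively only.

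The cost is a rewording of the outcome definitions and a different model for one secondary outcome. No new data are needed. With only 15 practices, the added cluster-level terms for the strata use up a few degrees of freedom.

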#### Outcomes from the evaluation questionnaire one week after consultation

To evaluate whether the SeMaS was discussed, and which actions were undertaken with the patient, an evaluation questionnaire was newly developed. Patients will be asked whether the SeMaS profile was discussed and which of the psychosocial aspects from SeMaS were covered during the consultation. Current self-management activities, and details of whether the patient received information, advice or referral to interventions for lifestyle or self-care, will also be covered in the questionnaire. The participating patients will receive the questionnaire one week after the consultation. These data will be compared in the intervention and control arm.

By triangulation of the data from the medical records, the evaluation questionnaire and the SeMaS profile, we will assess the number and type of SeMaS dimensions discussed with the patients related to the SeMaS scores on these various dimensions. More explicitly, per dimension we will assess whether this was a barrier in the profile, and whether it is mentioned in the medical record and the evaluative questionnaire. If so, this will be scored as proof of attention. We will assess the percentage of patients with a barrier and proof of attention for that dimension/barrier.

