In other fields of research, especially human genetics, the concept of personalized medicine has been introduced [19]. In the field of genetics, patients are genetically screened, and subsequently receive treatment that is adapted to their genomic profile. In psychology, treatment is adjusted to psychological characteristics and thus, person-centered [20-22]. We applied the concept of personalization to self-management support. Here, personalization is defined as adjusting the self-management support to the individual characteristics of the patient. For example, in the case of low self-efficacy, the practice nurse and patient make an individual care plan with small steps in goal setting to enhance the self-efficacy of the patient. Current generic self-management measures include the patient activation measure (PAM-13), which measures the current level of self-management and the Health Education Impact Questionnaire (heiQ), measuring the outcome of an intervention or education program [23,24]. However, there was no generic instrument available to identify factors that could hinder successful self-management. For this purpose, we developed a self-management screening questionnaire (SeMaS), as described below. Providing patients with personalized self-management support, we expect the patient-activation level to increase, which subsequently has a positive effect on health-related lifestyles, knowledge, skills, and the ability to take care of the chronic condition. This in turn will positively influence overall health and wellbeing. The SeMaS questionnaire will provide specific information about the abilities and possible barriers for self-management. Using a manual, the healthcare provider will have a starting point to influence possible barriers and stimulate self-management. This is shown in the logic model in Figure 1.

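### The proof-of-attention percentage leaves out patients without the barrier, so on its own it cannot tell tailored attention from a general rise in psychosocial discussion

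*Protocol article*

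**What the plan says.** All references are to the protocol article.

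- *Background* gives the concept: "personalization is defined as adjusting the self-management support to the individual characteristics of the patient". *Self-management support* turns it into an instruction for the intervention arm: "Practice nurses are instructed to adjust the delivery of care to the profile".
- *Outcomes from the evaluation questionnaire one week after consultation* describes the data: "Patients will be asked whether the SeMaS profile was discussed and which of the psychosocial aspects from SeMaS were covered during the consultation". The questionnaire goes to all participating patients, and its results are to be compared between arms.
- The same section then combines medical records, questionnaire and profile with a broad aim: "we will assess the number and type of SeMaS dimensions discussed with the patients related to the SeMaS scores on these various dimensions".
- The next sentences make that aim concrete. The first condition concerns the profile: "per dimension we will assess whether this was a barrier in the profile". The second is that the dimension also appears in the patient's record and questionnaire answers. For a dimension that meets both, the rule reads "If so, this will be scored as proof of attention". The only summary then named is "We will assess the percentage of patients with a barrier and proof of attention for that dimension/barrier".
- *Outcomes* plans to relate medical-record process data (care plans, self-monitoring, referrals and others) to the baseline SeMaS results. *Qualitative outcomes* plans interviews with intervention-arm professionals on the use of SeMaS.
- *Self-management support* states that control patients also complete the questionnaire, with no feedback to them or their nurse. Barrier status is therefore known in both arms.

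**The concern.** If support is adjusted to the profile, attention to a dimension should depend on whether it is a barrier for that patient. Showing this takes two rates: how often the dimension is raised when it is a barrier, and how often when it is not. The broad aim allows for both. The spelled-out scoring rule keeps only the first, because discussion with a patient who lacks the barrier is never scored.

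The alternative explanation is realistic. Under *Training and support of practice nurses in the intervention arm*, intervention staff receive a two-hour training session, a manual and practice visits; control practices are trained a year later. Such a package could lead nurses to talk more about psychosocial topics with everybody. The named percentage would then rise in the intervention arm although nothing had been tailored.

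What is at stake is how the process results are read, and so how well the trial can describe whether the personalised element was delivered.

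**Working it through.** The plan gives no figure for this measure, so there is nothing to reproduce. The check is algebraic, followed by an illustration on assumed rates.

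**Notation, for one dimension**
- p = proportion of patients with the barrier
- s = proportion with the dimension discussed among patients with the barrier
- f = proportion with the dimension discussed among patients without the barrier

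**The named percentage**
- Denominator patients with the barrier: s
- Denominator all patients: p × s

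Neither form contains f. Tailoring shows in s − f, which does.

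**Illustration (p, s and f are assumed; the article gives none)**

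| Pattern | s | f | Percentage, barrier denominator | Percentage, all patients (p = 0.1 / 0.3 / 0.5) | s − f |
|---|---|---|---|---|---|
| Usual discussion | 0.30 | 0.30 | 30% | 3% / 9% / 15% | 0.00 |
| Raised with everyone alike | 0.80 | 0.80 | 80% | 8% / 24% / 40% | 0.00 |
| Tailored | 0.80 | 0.20 | 80% | 8% / 24% / 40% | 0.60 |

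1. The second and third rows have the same named percentage at every p, while s − f is 0 against 60 points.
2. From the first row to the second, the percentage rises by 50 points (30% to 80%) with no tailoring in either.
3. With all patients as denominator and s fixed at 0.80, moving p from 0.1 to 0.5 moves the figure from 8% to 40% with no change in what nurses do.

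**What the other planned counts add.** The overall share of patients with the dimension discussed is p × s + (1 − p) × f. At p = 0.3 it is 0.80 when raised with everyone and 0.24 + 0.70 × 0.20 = 0.38 when tailored, so it does separate these two patterns. If p, s and this share were all reported per dimension on the same scoring, f would follow: (0.38 − 0.24)/0.70 = 0.20. But the article describes proof of attention by mention in the record and the questionnaire, whereas the comparison by arm is of questionnaire data. The two cannot safely be combined in this way.

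**Precision of the contrast.** Inputs are 750 patients and 33% dropout (*Sample size*), and an assumed prevalence of 30%.
- Analysable patients: 750 × 0.67 = 502.5, or about 250 per arm, of whom about 75 have the barrier and 175 do not.
- Standard error of the between-arm difference in (s − f), at the worst case of 0.5 for every proportion: √[2 × (0.25/75 + 0.25/175)] = √0.00952 = 0.098, or 9.8 points per dimension, before any allowance for clustering.

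The 33% is the article's general dropout figure; loss to the one-week questionnaire may differ. The documents give no intraclass correlation for this contrast, so no design effect is applied.

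**The case against.** A reader might infer that this percentage is the only planned measure of delivery, and that the trial therefore cannot show that support was personalised. The documents do not support that. Patients are asked directly whether the profile was discussed and which aspects were covered, and the answers are compared between arms. The broad aim of relating dimensions discussed to SeMaS scores is not limited to patients with a barrier. Process data are related to the baseline profile, and professionals are interviewed. These sources give partial evidence, and the data for the full contrast will exist.

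Three further objections carry weight.

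- **The manual tells nurses what to do where a barrier exists.** The article nowhere tells them to stay silent on other dimensions. This stands: discussion without a barrier is not a protocol breach, and the barrier-only percentage is a reasonable measure of whether barriers were addressed. It is not a measure of tailoring.
- **A low percentage would still reveal that barriers were not acted on.** This also stands. What the figure misses is indiscriminate discussion.
- **The contrast would not attribute a PAM-13 gain to personalisation.** Correct. The intervention bundles training, visits, reports and patient feedback against usual care, and no process contrast separates those parts.

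It can also be said that denominators and models belong in the separate analysis plan that the *Analysis* section mentions. That is fair for the denominator and the model. It does not cover the scoring rule, which the article states and which is narrower than the aim just before it.

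**Conclusion.** The point holds for the named statistic. With either denominator it ignores discussion in patients without the barrier, so taken alone it cannot separate tailored attention from a general rise in discussion. That follows from the algebra and needs no assumed rates. The size shown (80% for both patterns, against a contrast of 0 or 60 points) is illustrative. The dependence on prevalence arises only if the denominator is all patients.

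The reach is limited. This is a secondary process measure, other planned data partly fill the gap, and the PAM-13 analysis is not affected. At a standard error of about 9.8 points per dimension before clustering, a large contrast could be seen and a small one could not. That rests on 30% prevalence and about 250 analysable patients per arm.

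**What to change.** 1. For each SeMaS dimension and each arm, report the percentage of patients with the dimension discussed among those with that barrier and among those without it, and the difference. Score a mention in the same way in both groups.
2. Compare this difference between arms (arm × barrier) in one model across dimensions that allows for practice and for repeated dimensions within a patient. Name it as the process measure of tailoring.
3. Keep the barrier-only percentage as a descriptive figure, with patients having that barrier as the stated denominator.
4. Present the no-barrier rate as context for tailoring, not as an error rate, and do not use the contrast to explain a PAM-13 result.

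The cost is a few lines in the analysis plan and one additional secondary process analysis. Profile, questionnaire and record data are already planned for participating patients in both arms, so no new data are needed.
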